##### Syndrome scores

The PCOS syndrome scores will be recorded before and after treatment to assess whether the treatment improved the patient’s signs of PCOS.

The TCM syndrome scores will be recorded by the same professor once a week to adjust the acupuncture and herbal treatment [28] and evaluate the improvement of the patients’ TCM syndromes.

##### Blinding assessment

Assessment for patients’ blinding was conducted after the last treatment session. All patients will be asked to guess whether they have received TA or SA.

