According to the textbook *Acupuncture and Moxibustion* [26], and taking opinions from Chinese acupuncture experts, the essential acupuncture points selected are as follows: RN4 (*Guanyuan*); EX-CA1 (*Zigong*); ST29 (*Guilai*); ST36 (*Zusanli*); and SP6 (*Sanyinjiao*). The additional individualized acupuncture points will be chosen by the practitioners according to the patterns of identification: (1) spleen–kidney Yang deficiency plus RN6 (*Qihai*), RN12 (*Zhongwan*), ST25 (*Tianshu*); and (2) liver–kidney Yin deficiency will add with bilateral KI3 (*Taixi*), KI6 (*Zhaohai*). According to the menstrual cycle, the follicular phase will use the acupuncture points bilateral KI3 (*Taixi*) and KI6 (*Zhaohai*); the ovulatory phase will use the acupuncture points bilateral LR3 (*Taichong*), SP10 (*Xuehai*), PC6 (*Neiguan*), and DU20 (*Baihui*) (Table 2). A placebo device [27] will be applied in both groups for better implementation of blindness. The schematic diagram of acupuncture treatment is shown in Fig. 2. The acupuncture treatment in both groups will take 30 min per session, twice per week, from the third day of menstruation to the third day after ovulation for three menstrual cycles. Acupuncture treatments will be stopped upon a positive pregnancy test. The test will be done on the 14th day after each ovulation.

**Table 2 Tab2:** Acupuncture point selection

Point	Location
RN4 (*Guanyuan*)	On the lower abdomen at the anterior midline, 3 *cun* below the umbilicus
EX-CA1^a^ (*Zigong*)	On the lower abdomen, 4 *cun* below the center of the umbilicus and 3 *cun* lateral to the anterior midline
ST29^a^ (*Guilai*)	1 *cun* cranial to the pubic bone and 2 *cun* lateral of the midline
ST36^a^ (*Zusanli*)	At the anterior aspect of the leg 3 *cun* inferior to ST35 (*Dubi*) on the line connecting ST35 (*Dubi*) to ST41 (*Jiexi*)
SP6^a^ (*Sanyinjiao*)	On the tibial aspect of the leg posterior to the medial border of the tibia, 3 *cun* superior to the prominence of the medial malleolus
Syndrome 1	
RN6 (*Qihai*)	With the patient supine, the point is halfway between the center of the umbilicus and RN4 (G*uan yuan*)
RN12 (*Zhongwan*)	On the upper abdomen at the anterior median line, 4 *cun* above the umbilicus
ST25^a^ (*Tianshu*)	On the upper abdomen 2 *cun* lateral to the center of the umbilicus
Syndrome 2 and phase 1	
KI3^a^ (*Taixi*)	On the posteromedial aspect of the ankle in the depression between the prominence of the medial malleolus and the calcaneal tendon

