#### Sham acupuncture group

The procedure and duration of treatment in the SA group will be identical in the TA group except the needles (0.25 × 25 mm, blunt tip, provided by Wuxi Jiajian Medical Instrument Co. Ltd., China) are blunt tip and there will be no skin penetration or manual stimulation.

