### Outcome measures

Outcomes will be collected at baseline, each menstruation, after three menstrual cycles of treatment, and follow-up at six months after the completion of the treatment. The overview of the outcome measurement at the different time points is shown in Table 3.

**Table 3 Tab3:** Overview of study visits

	Screening and baseline visit	Menstrual cycles			Six months after the last acupuncture treatment
		1st	2nd	3rd	
General condition ^a^	√				
Gynecological examination	√				
Fasting blood samples for sex hormone ^b^, FINS, FBG, HbA1c	√			√	
Transvaginal ultrasound	√	√	√	√	
Pregnancy test (blood β-HCG)				√	
Treatment record ^c^		√	√	√	
Questionnaire ^d^	√			√	
Telephone follow-up ^e^					√

^a^General condition include age, BMI, menstrual and obstetrical histories

^b^Sex hormones include: E2, T, P, FSH, LH, PRL, DHEAS, SHBG

^c^Treatment record includes date and adverse events

^d^Questionnaire includes the PCOS and TCM syndrome scores

^e^Inquires if the participants were pregnant

*E2* estradiol, *T* total testosterone, *P* progesterone, *FSH* follicle-stimulating hormone, *LH* luteinizing hormone, *PRL* prolactin, *DHEAS* dehydroepiandrosterone sulfate, *SHBG* sex hormone-binding globulin, *BMI* body mass index, *FINS* fasting insulin, *FBG* fasting blood-glucose, *HbA1c* glycated hemoglobin

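### The only patient blinding guess comes after the last session, when pregnancy in cycles 1 and 2 is already known, so it cannot separate sham credibility from known outcome

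*Protocol article*

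**What the plan says.** Under Blinding assessment, the protocol article sets one time point: the assessment of patients' "blinding was conducted after the last treatment session". The question is described in one sentence: "All patients will be asked to guess whether they have received TA or SA". Neither the text nor Table 3 shows an earlier assessment.

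Under Interventions, sessions are given "twice per week, from the third day of menstruation to the third day after ovulation for three menstrual cycles". On pregnancy testing, the same section says: "The test will be done on the 14th day after each ovulation". It also says: "Acupuncture treatments will be stopped upon a positive pregnancy test". Under Ovulation rate, every cycle is followed by basal body temperature or by three to four ultrasound scans.

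The arms differ in what the patient can feel. Manual needles are inserted and manipulated every 10 minutes to maintain the deqi sensation. In the sham arm "there will be no skin penetration or manual stimulation".

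**The concern.** The trial claims patient blinding, and the end-of-treatment guess is the only evidence for it that the article describes. A woman who conceives in cycle 1 or 2 can be recognised as having had her last session only once her test is positive, so she guesses knowing that she is pregnant. A woman who reaches cycle 3 knows that two cycles failed, and has followed her own ovulation in each.

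If manual acupuncture works, more women in that arm will know that they conceived, and some will take this as a sign of real needles. The guess can then differ between arms even if every patient found the sham convincing. If sensation did reveal the allocation, the same data could not show it. With a sham that lacks penetration and manipulation, that is the question the check most needs to answer.

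**Working it through.** The article gives no figure for the blinding assessment, so there is none to reproduce. The check sets out what each woman knows when asked, then illustrates the size.

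**Who knows what, from Interventions and Ovulation rate**
- Conceived in cycle 1 or 2: the positive test has ended her sessions, so the pregnancy is known.
- Reached cycle 3: two failed cycles are known, with ovulation findings. The last session falls by day 3 after ovulation and the test on day 14, so 14 - 3 = 11 days later at least. If asked at that session, she does not know the cycle-3 result. The article does not say whether the question comes before or after that test.

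**Inputs**
- Pregnancy rates of 76% (manual) and 40% (sham), and 43 women per group, from the sample size section.
- Assumption: constant conception probability over three cycles.
- Assumption: women who know they are pregnant guess true acupuncture 80% of the time, others 30-50%, regardless of arm. This represents a perfectly convincing sham.

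**Step 1: known pregnant by the end of cycle 2**, 1 - (1 - p)^(2/3)
- Manual: 1 - 0.24^(2/3) = 0.614, about 26 of 43.
- Sham: 1 - 0.60^(2/3) = 0.289, about 12 of 43.

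**Step 2: probability g of guessing true acupuncture**
- Manual: 0.614 × 0.8 + 0.386 × 0.3 = 0.607; with 0.5 in place of 0.3, 0.684.
- Sham: 0.289 × 0.8 + 0.711 × 0.3 = 0.444; with 0.5, 0.587.
- Gap: 0.607 - 0.444 = 0.16, or 0.684 - 0.587 = 0.10.

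**Step 3: Bang index**, 2 × P(correct) - 1 in each arm
- Manual (2g - 1): 0.21 to 0.37.
- Sham (1 - 2g): 0.11 to -0.17, in the same order.
- Overall correct: (0.607 + 1 - 0.444)/2 = 58%, or (0.684 + 1 - 0.587)/2 = 55%.
- Chance of a significant guess-by-arm difference at 43 per group: about 32% or 15%.

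**Sensitivity to the share guessing from outcome.** Suppose a share f guesses strictly from the cycle 1-2 result and the rest guess at random:

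| f | True guesses, manual v sham | Bang, manual / sham | Correct overall | Chance of significance |
|---|---|---|---|---|
| 1 | 61% v 29% | 0.23 / 0.42 | 66% | 87% |
| 0.75 | 59% v 34% | 0.17 / 0.32 | 62% | 63% |
| 0.5 | 56% v 39% | 0.11 / 0.21 | 58% | 32% |
| 0.25 | 53% v 45% | 0.06 / 0.11 | 54% | 11% |

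**If the arms do not differ.** At 40% in both arms, the step 2 assumptions give g of 0.444 to 0.587 in each. Overall correct guesses are then 50%, although the arm-specific indices still move away from zero (manual -0.11 to 0.17, sham 0.11 to -0.17).

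**The case against.** The strongest reply is that the consequence is small. The primary outcome is a blood β-HCG result, and the Data analysis section names no analysis that uses the guess. Women with previous acupuncture are excluded and the placebo device is used in both arms, which supports the sham's credibility. All of this stands and limits the severity. It does not give the trial a blinding check free of known outcome.

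A reader might infer that the guess measures outcome instead of sham credibility, or that it will show broken blinding if manual acupuncture works. The documents support neither. The guess mixes the two in an unknown proportion. Under the illustrative 80% and 30-50% guess rates, a significant difference is less likely than not (15-32%), and a sham index at or below zero is not the usual picture of a failed sham. A reader might also put the full 76% v 40% into the calculation, but cycle-3 conceptions are not yet known if the question is asked at the last session.

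Nor can it be inferred that the question lacks a do-not-know option. The article describes the question in one sentence, and the response form is not shown.

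An early guess has its own weakness: it misses unblinding that builds up over three cycles of felt or absent stimulation. That is a sound reason against replacing the late guess.

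Finally, Table 3 appears to mark the β-HCG test in the third cycle only, which does not match testing after each ovulation in Interventions. The two must be reconciled. The argument here follows the Interventions text, which also ties the end of sessions to a positive test.

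**Conclusion.** The point holds in limited form. Followed as written, the plan yields one blinding result that is tied to the primary outcome, because those who conceived in cycles 1-2 know it and the others know that those cycles failed.

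With a perfectly convincing sham, outcome knowledge alone could produce a gap of 10-16 percentage points in guesses of true acupuncture. This rests on constant per-cycle conception, the protocol's hypothesised rates and assumed guess rates. The document gives no basis for the share of women guessing from outcome, and across the range shown the chance of a significant guess-by-arm difference runs from 11% to 87%. The distortion of the between-arm comparison arises when pregnancy rates differ, which is when readers will most want the check. What is weakened is the evidence on blinding. Measurement of the primary endpoint, the sample size and the power are unaffected.

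**What to change.** 1. Add one guess in cycle 1, after the first sessions and before any ovulation or pregnancy result, and record the reason for the guess. If the sham is convincing and women guess at random, the expected Bang index is 0 in both arms.
2. Keep the end-of-treatment guess beside it, and in cycle 3 ask it before the β-HCG result is known.
3. Report the late guess by arm and by known pregnancy status, with the Bang index and 95% CI in both arms.

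The cost is one extra question at an existing visit. It may prompt some women to think about their allocation. Because the early guess cannot capture later unblinding, both time points are needed.

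The article expected the last inclusion in February 2019 and appeared in September 2019. For women already treated, only the report by known pregnancy status is possible, and it needs no new visit.

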##### Sex hormones and IRI

The fasting blood samples will be drawing in the third day of menstruation before and after treatment by the nurse. The chemiluminescence immunoassay (CLIA) will be used to determine serum sex hormone levels include estradiol (E2), T, progesterone (P), FSH, LH, prolactin (PRL), dehydroepiandrosterone sulfate (DHEAS), sex hormone-binding globulin (SHBG), and fasting serum insulin (Model: Switzerland ELECSYS2011). The oxidase method will be used to measure fasting plasma glucose through automatic biochemical analyzer (Model: Japan OLMPUS AU 400). These tests will all performed by the Shuguang Hospital Medical Testing Center.

The gold standard for investigating and quantifying insulin resistance is the “hyperinsulinemic euglycemic clamp” [29], but it rarely performed in clinical because of the invasive. The insulin resistance index (HOMA-IR) is a simpler test and is calculated by the equation (HOMA-IR = fasting blood glucose × fasting insulin/22.5).

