### Sample size, randomization, and blinding

Due to the lack of sufficient preliminary studies, it is difficult to determine adequate sample size. According to the studies [23, 24], we hypothesize that the pregnancy rate after MA is 76% and the pregnancy rate after SA is 40%. The calculation equation we used was α = 0.05, 1-β = 0.80 and we determined that a sample size of 36 patients in each group would be sufficient to detect the statistical difference between the two groups, allowing for a 20% withdrawal rate. We will plan to enroll a total of 86 participants with 43 participants in each group. According to the random number sequence generated by Excel, the patients will be randomly divided into either the MA group or the SA group in a 1:1 ratio. We set the blind code in the case for remaining blind when the patients have the adverse effects. The random code and blind code will be conducted by a “third party” independent of the study using opaque envelopes. The envelopes will be sealed and shuffled and the assignment records will not be disclosed until the end of the study. Trial participants, formula doctor, outcome assessors, and data analysts will be blinded to the treatment allocation to minimize potential sources of bias. Because of the special nature of acupuncture, only acupuncturists will not be blinded to the treatment allocation.

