### Data analysis

All statistical analyses of the data will be performed using SPSS program V.21.0 (SPSS Inc., Chicago, IL, USA). A *P* value < 0.05 will be considered statistically significant. For cases in which we do not finish all the treatment, we select intention-to-treat (ITT) analysis to avoid the effects of crossover and drop-out. Measured data will be expressed as mean ± SD ($$ \overline{x} $$ ±s) if it obeys a normal distribution or approximate normal distribution. Median (interquartile range [IQR]) will be used if the data do not obey the normal distribution and count data will be expressed in terms of the number of cases. We will use chi-square tests for categorical data and two-sample t-test or Wilcoxon rank sum test for continuous data, according to whether the data are normally distributed. The variance analysis will be performed for the difference between the two groups and within the group. The stratified analysis will be performed to control the confounding factor if necessary. Data analysis will be conducted by statisticians who are independent of the research team.

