## Discussion

Acupuncture therapy is a major component of TCM and is increasingly widely used because it is non-invasive and has fewer side effects [30–32]. The drugs for ovulation induction may lead to adverse reactions such as OHSS and multiple pregnancy. Compared with previous studies, we combined the TCM therapy with scientific and rigorous experimental design to explore the effect of MA on infertile women with PCOS. The selection of acupoints and herbs is based on the syndrome differentiation and the period of the female menstrual cycle in order to adequately demonstrate the dialectical treatment of TCM.

In terms of the treatment period, the acupuncture treatment starts on the third day of menstruation to the third day of ovulation; therefore, acupuncture can be fully utilized to promote the development and discharge of follicles and can avoid the risk if the patient is pregnant.

The evidence for long-term efficacy of acupuncture in patients with PCOS is not sufficient. However, a neurological study [33] showed that though SA and placebo were as effective as TA in terms of reduction of symptoms and objective physiological outcomes, verum acupuncture was superior to SA in producing improvements in both peripheral and brain neurophysiological outcomes. Pregnancy is the ultimate indicator of infertility treatment and insulin resistance (IR) is a pathological condition in which cells fail to respond normally to the insulin [34–36]. Of people with PCOS, 50–80% may have IR at some level [37]. IR is closely related to the pathogenesis of PCOS [38]. Therefore, we select the pregnancy rate, ovulation rate, sex hormones, and IRI as indicators of efficiency of the trial. We expect to discover that MA can be more helpful for promoting follicular development, adjusting menstrual cycle, and increasing pregnancy rate in infertile women with PCOS.

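### Post-treatment hormones and insulin resistance are sampled on day 3 of menstruation, so the between-arm tests are conditional on not being pregnant, which the plan expects to differ by arm

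*Protocol article*

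**What the plan says.** Protocol article, Sex hormones and IRI: "The fasting blood samples will be drawing in the third day of menstruation before and after treatment by the nurse". The rule covers the sex hormones and the fasting insulin and glucose from which HOMA-IR is calculated. Table 3 marks this blood draw at baseline and once more, by column order in the third cycle.

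Sample size, randomization, and blinding: "we hypothesize that the pregnancy rate after MA is 76% and the pregnancy rate after SA is 40" (both per cent), with 43 women per arm.

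Primary outcome and Interventions: pregnancy is tested by blood β-HCG 14 days after ovulation, and a positive test ends acupuncture.

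Data analysis: "two-sample t-test or Wilcoxon rank sum test for continuous data", with the choice depending on normality, alongside a general intention-to-treat statement.

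Discussion: "we select the pregnancy rate, ovulation rate, sex hormones, and IRI as indicators of efficiency of the trial".

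No section gives another sampling time for women who are pregnant, or says how they enter the hormone and HOMA-IR comparisons.

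**The concern.** A day-3 menstrual sample needs a menstruation. A woman who is pregnant when the post-treatment sample falls due generally does not have one, so reaching the primary outcome takes her out of the hormone and HOMA-IR comparison. The trial is built on the hypothesis that this happens more often under MA. If so, the two groups of women with a value are no longer the groups that randomisation formed. They are selected on a post-randomisation event that treatment affects.

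If the markers are related to fertility, the remaining MA women would be a less fertile selection than the remaining SA women. A null or unfavourable hormone result could then arise because MA raised pregnancy, and it could not be told apart from a true lack of hormonal effect. The Discussion counts these markers among the indicators of efficacy, so the result would be read as evidence on whether MA works.

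**Working it through.** **Inputs.** From the protocol: pregnancy 76% (MA) and 40% (SA); α 0.05, power 0.80; 36 per group, 20% withdrawal, 43 per group enrolled; sampling on day 3 of menstruation. Assumed: two-sided α; a constant chance of conception per cycle for the alternative timings; a correlation ρ of 0.3 to 0.5 between marker and fertility.

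**The plan's own figure.** For 76% v 40%, the two-proportion formula gives 29 per group without continuity correction and 34 with it, close to the stated 36. Then 34/0.8 = 42.5, rounded up to 43, the number enrolled. The rates are used below as the plan's own hypothesis.

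**Women who can be sampled after cycle 3 (main reading).** Share = 1 − pregnancy rate.
- MA: 1 − 0.76 = 0.24; 43 × 0.24 = 10.3
- SA: 1 − 0.40 = 0.60; 43 × 0.60 = 25.8

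These are upper limits, because withdrawals and non-pregnant women without menses come off them. With 20% independent withdrawal: 0.24 × 0.8 = 19% and 0.60 × 0.8 = 48%.

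**Other readings of the timing**, constant conception rate per cycle:
- Sample at the menses that opens cycle 3, after two of three cycles: 0.24^(2/3) = 0.39 and 0.60^(2/3) = 0.71.
- Rates that include the six-month follow-up, about nine cycles, sample after three: 0.24^(1/3) = 0.62 and 0.60^(1/3) = 0.84.

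**Size of the distortion with no true hormone effect.** Treat fertility as a standard normal variable and let the women with the highest values conceive. The mean fertility of the remaining lowest share q is −φ(z_q)/q, where z_q is the q-quantile.
- q = 0.24: −0.311/0.24 = −1.295
- q = 0.60: −0.386/0.60 = −0.644
- Difference: −0.651 SD. Multiplied by ρ = 0.3 and 0.5, this is −0.20 and −0.33 SD for the marker.

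The same steps for the other readings:

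| Reading | Share sampled, MA v SA | Fertility gap (SD) | Marker gap (SD), ρ 0.3 to 0.5 |
|---|---|---|---|
| After cycle 3 | 24% v 60% | 0.65 | 0.20 to 0.33 |
| Menses opening cycle 3 | 39% v 71% | 0.51 | 0.15 to 0.26 |
| Rates include follow-up | 62% v 84% | 0.33 | 0.10 to 0.16 |

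**Error rate.** Simulating the main reading at 43 per arm, with a t-test on the sampled women and no true effect, a nominal 5% test rejects about 8% (ρ = 0.3) to 15% (ρ = 0.5) of the time. At ρ = 0 it stays near 5%.

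**Precision.** The difference detectable with 80% power is 0.61 SD at 43 v 43 and 1.07 SD at 10 v 26. The first figure ignores withdrawals, and the trial was not sized for hormones, so this shows only how much information is lost.

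**The case against.** Five points on the other side have weight.

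- The shares of 24% and 60% are complements of planning rates that the protocol itself introduces as resting on scant preliminary work. A reader might infer that the tests will in fact compare 24% of one arm with 60% of the other. The documents do not support that. If MA leaves pregnancy unchanged, pregnancy creates no imbalance, and the timing readings above widen the range. This stands.
- Not pregnant is not the same as sampled. The inclusion criteria admit women with oligomenorrhoea or amenorrhoea, so poor responders may also lack a day-3 sample, and that selection can run the other way. Conversely, a woman with an early loss may menstruate again and be sampled. The documents give no figure for either. So the size of the bias is not established, and it is too strong to say that every woman who conceives is lost.
- A reader might infer that the plan prescribes a complete-case test, or that intention-to-treat is impossible for these outcomes. The Data analysis section says neither, and missing-data rules may sit in a document not shown. This limits the charge but does not remove it. The sampling rule and the two-sample test are stated here, and a day-3 menstrual value does not exist for a woman who is pregnant, so there is no unobserved value to impute.
- One might repair the test by ranking all randomised women and giving those pregnant the best rank. At the planned rates and with no hormone effect, that test rejects about 85% to 91% of the time for ρ from 0.5 down to 0. It mostly re-tests the primary outcome and is not evidence about hormones.
- The point does not extend to the PCOS score, which is recorded before and after treatment with no menstruation rule.

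**Conclusion.** The concern holds for the post-treatment sex hormones and HOMA-IR. As written, their between-arm comparison is conditional on not being pregnant, and the trial's own hypothesis makes that condition unequal between arms.

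Under each timing reading considered, pregnancy alone leaves fewer MA than SA women available if the planned rates hold. The ratio of shares runs from 24% v 60% to 62% v 84%. The resulting distortion of about 0.10 to 0.33 SD against MA rests on the assumed correlation of 0.3 to 0.5 and on pregnancy being the only reason for a missing sample. It is an illustration of scale, not an estimate.

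Only secondary outcomes are affected, and the primary pregnancy comparison is untouched. The change should be made, but the point does not call the trial's main conclusion into question.

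**What to change.** In Sex hormones and IRI and in Data analysis, state that post-treatment hormone and HOMA-IR values are reported descriptively by arm, as conditional on not being pregnant at sampling. Give by arm the number sampled and the reason for no sample: pregnant, no menses, withdrawn. Attach no between-arm P value or efficacy claim to these values. Amend the Discussion so that sex hormones and IRI are not used as between-arm indicators of efficacy. Do not substitute a composite rank test as evidence about the hormones.

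The cost is wording only, with no new samples; the change is best made before unblinding. The small downside is that the trial gives up a confirmatory between-arm comparison of hormones and HOMA-IR.
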